# Randomized, controlled, parallel-group prospective study to investigate the clinical effectiveness of early insulin treatment in patients with latent autoimmune diabetes in adults

**DOI:** 10.1186/1472-6823-8-8

**Published:** 2008-07-24

## Abstract

**Background:**

Latent autoimmune diabetes in adults [LADA] is a type 1 diabetes that is slowly developing. This means many people are treated as having type 2 diabetes at diagnosis as they are adults who are not immediately insulin dependent. LADA can be distinguished from type 2 diabetes by antibody tests. Patients who are antibody positive have an autoimmune reaction which is similar to that of type 1 diabetes and is not found in type 2 diabetes. We would like to examine the best way of treating LADA in the early phase of the conditions, with tablets (similar to type 2 diabetes) or with insulin (similar to type 1 diabetes).

**Methods/design:**

This is an open parallel group prospective randomised trial. Participants need to have a GAD antibody test results of 101 WHO units or more and a diagnosis of diabetes not requiring insulin at diagnosis. Participants will need to have been diagnosed within 12 months and not treated with insulin at study entry. They will be randomised to receive either insulin (NovoMix 30) or tablets (diet treated followed by metformin followed by glitazone (with or without metformin) followed by insulin). Primary outcome assessment will be for change in HbA1c and change in fasting C-peptide over 24 months. Secondary outcome measures will include Quality of life, GAD antibody levels, adverse events, inflammatory markers, insulin resistance, and markers of the metabolic syndrome.

**Discussion:**

This study seeks the best treatment for early LADA in terms of maintaining glycaemic control and maintaining natural insulin production.

**Trial registration:**

ISRCTN63815121

## Background

### Type 1 diabetes

Diabetes mellitus is the most common endocrine disease. There are two main types of diabetes, type 1 and type 2. Although type 1 diabetes often develops in young people, it can occur at any age. Type 1 diabetes is caused by an autoimmune process resulting in a selective destruction of the pancreatic insulin-secreting β-cells. The destruction of β-cells leads to hyperglycaemia due to a lack of insulin. The immune changes are reflected by the presence of islet cell antibodies (ICA) and antibodies to glutamic acid decarboxylase (GAD) [1]

### Type 2 diabetes

Type 2 diabetes most often develops in adults and is characterized by insulin resistance and subsequent insulin deficiency. Approximately 10% of patients with type 2 diabetes have antibodies to GAD and/or ICA and progress to insulin dependency [2,3]. The term LADA (latent autoimmune diabetes in adults) has been introduced to define adult diabetes patients who are initially non-insulin-requiring but with immune markers of type 1 diabetes, who progress to insulin dependency.

#### LADA

Latent autoimmune diabetes in adults is a type 1 diabetes which shows slow progression to insulin dependence instead of acute onset as is seen in 'classical' type 1 diabetes. It is an autoimmune condition unlike type 2 diabetes and therefore can be distinguished from type 2 by blood tests for antibodies.

## Methods/design

### Aims and objectives

To compare the effectiveness of treatment regimes for type 1 diabetes compared to regimes for type 2 diabetes in LADA.

#### Primary objectives

To examine the effect of standard treatment for type 1 (insulin [NovoMix 30] therapy) compared with standard treatment for type 2 diabetes (tablets), on (1) change in fasting serum C-peptide level over 24 months and (2) change in HbA1c level over 24 months in patients with LADA.

#### Secondary objectives

To assess the effect of standard type 1 treatment (insulin) on average number of times the fasting plasma glucose level is above 8 mmol/l (141 mg/dl), quality of life [ADDQol [12]], proportion of patients with insulin dependence (as judged by C peptide level below 0.38 ng/ml [13]), GAD antibody level, HOMA, hypoglycaemic events (particularly hypoglycaemic events), weight/blood pressure/total cholesterol and inflammatory markers in LADA patients compared to standard type 2 diabetes treatment.

### Design

This trial is a multi-centre open parallel group prospective randomised trial. Participants are recruited from their primary health care practitioner following a routine test for GAD antibodies. They are seen in secondary care at 3 centres in Wales (Swansea, Carmarthenshire and Cardiff). The protocol has been approved by the Multi-Centre Research Ethics Committee for Wales. Each recruited subject has to sign a consent form and give their consent to randomisation.

#### Intervention

Insulin arm: Patients will be given advice on diet and exercise and life style and will be started on NovoMix 30, one dose of 6 U at the evening/main meal. Dose will be adjusted in increments of 2–6 U depending on fasting glucose level [See Figure 1]. When total dose equals 16 U patient will be started on 4 units with breakfast and continue with 16 units with evening meal. Breakfast and/or evening meal dose will be adjusted where necessary at increments of 2–6 U depending on fasting and/or pre-evening meal glucose level. [See Figure 1 below]. Patient needs to keep a daily diary of insulin doses taken.

**Figure 1 F1:**
[figure not shown]
Insulin treatment.

All patients will see a dietician before insulin treatment is initiated. Patients will be contacted weekly by phone in the first month, fortnightly in the second month and once a month thereafter. Patients will monitor their blood glucose twice a day for 3 days of the week.

#### Tablet arm:

##### [Figure 2] Step 1

**Figure 2 F2:**
[figure not shown]
Standard treatment arm.

Patient's not treated with tablets will be given a 3 months trial of lifestyle modification including advice on diet, exercise and smoking. If HbA1_c _remains at 7% or above the patient will progress to step 2. Patients will be progressed to step 2 if their GP has already put them on metformin (put in at number of metformin tables that GP has recommended) or sulphonylurea or if their baseline HbA1_c _is above 8% (patients will start on one 500 mg tablet per day). This means that sulphonylurea will be discontinued in all patients. Patients on step 1 will be progressed to step 2 before the 3 month period if they have already had a 3 month period of diet before starting the study AND during phone contact they report to be symptomatic (thirst, fatigue, polyuria) and unwell. In these cases, patients may be invited to attend clinic before the 3 month period to be given metformin.

##### Step 2

Life style modification and Metformin. If the patient has a HbA1_c _of 7%–7.5% they start on 500 mg × 1 per day for the next 3 months. If the HbA1_c _is 7.6%–8.0% they would start the first week on 500 mg × 1 day and then for the remaining period of the three months will take 500 mg × 2 day. If the HbA1_c _is above 8.0% then patient will be on 500 mg × 3 per day. This will be titrated at the rate of 500 mg × 1 for the first week, 500 mg × 2 for the second week and 500 mg × 3 for the remaining time of the 3 month period. If unable to tolerate metformin then the participant will be given Glucophage SR and if unable to tollerate this they will then progress to Step 3. If HbA1_c _remains at 7% or above then those on 1 tablet per day will be moved to 2 tablets per day, those on 2 tablets per day will be moved to 3 tablets per day, those on 3 tablets per day will be move to maximum dose of 2 gms per day. If after 3 months the HbA1_c _is above 7% even with maximum dose, then progress to Step 3. If during telephone contact the patient report symptoms then they may be titrated up. In summary, patients will be have their HbA1c evaluated every 3 months and will be titriated accordingly.

##### Step 3

Life style modification and Glitazone [Rosiglitazone]. Patients with a HbA1_c _of 7% or above will be given 4 mg once per day for 3 months. If after a 3 month period the HbA1_c _remains at 7% or above then titrate to maximal dose of 4 mg twice per day with or without Metformin. If HbA1_c_remains at 7% or above for an additional 3 months then move to step 4. Therefore, glitazone monotherapy will be used if Metformin intolerant otherwise glitazone will be added to the metformin (as per standard practice). Before initiation of Rosiglitazone a repeat medical history will be taken with special emphasis on cardiovascular disease, if patients have a history of cardiovascular disease (defined as IHD, PVD) they will not be initiated on Rosiglitazone but will move directly to Step 4 (insulin). Patients on rosiglitazone will be monitored using the adverse events form, for symptoms of heart disease specifically for chest pain and shortness of breath. Any adverse events suggestive of heart disease will result in Rosiglitazone being discontinued and the patient moving to step 4.

##### Step 4

Life style modification and insulin therapy (oral agents will be stopped). Titration will be based on fasting blood glucose level (as given in Figure 1). The initiation of insulin will the same as for the insulin arm and will follow the protocol detailed above.

All tablet treated patients will be asked to keep a diary of daily medication and record blood glucose levels weekly.

All changes in medication will be notified to the patients GP.

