#### Exclusion criteria

1. Pregnant or breast-feeding females and females who plan pregnancy or breast-feeding during the course of the study.

2. A history of:

▪ Diabetes that is a result of pancreatic injury, or secondary forms of diabetes, e.g., Cushing's syndrome and acromegaly.

▪ Acute metabolic diabetic complications such as ketoacidosis or hyperosmolar state (coma) within the past 6 months

3. Acute infections, which may affect blood glucose control within 4 weeks prior to visit 1.

4. Malignancy including leukaemia and lymphoma (not including basal cell skin cancer) within the last 5 years.

5. The patient has a known immune deficiency from any disease, or a condition associated with an immune deficiency.

6. The patient is receiving immunosuppressive or immunomodulating agents or cytotoxic therapy, or any medication that, in the opinion of the site investigator, might interfere with the study.

7. Any of the following significant laboratory abnormalities:

• Patients with severe renal failure as defined previous renal transplant or currently having renal dialysis or GFR < 30.

• Clinically significant laboratory abnormalities, confirmed by repeat measurement, that may interfere with the assessment of safety and/or efficacy of the study drug, other than hyperglycemia and glycosuria at visit 1.

• Severe ketonuria (+++ on urine sticks testing; ++ on repeated urine sticks testing).

8. The patient is a known or suspected drug abuser.

9. The patient has chronic hepatitis or liver cirrhosis, or any other chronic liver disease.

10. The patient is known to test positive for hepatitis B antigens or hepatitis C antibodies

11. The patient is known to test positive for HIV antibodies.

12. The patient has any significant diseases or conditions, including psychiatric disorders and substance abuse that, in the opinion of the site investigator, are likely to affect the patient's response to treatment or their ability to complete the study.

13. The patient has chronic haematological disease.

14. The patient has had a severe blood loss (≥ 400 mL, e.g., blood donation) within 2 months before the first dosing of the study medication.

15. The patient has known proliferative retinopathy.

16. Patient has had stage 3–4 heart failure.

17. The patient is participating in another research study which may affect the results of this trial.

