### Withdrawn from study

A patient is considered to have withdrawn from the study if they completely withdraw from the study, i.e.:

- Move and do not provide a new address or contact number

- Miss more than 3 visits without contacting the study centre.

- Die

However, if they discontinue treatment but continue participate in data collection they will not be considered to have withdrawn, i.e:

- Want to change therapy due to personal reasons but attend a termination visit.

- Experience a serious adverse event that in the medical judgement of the site investigator and for the best interest of the subject, are grounds for discontinuation, but attend a termination visit.

- Withdraw consent but give consent to the use of the data collected to date.

- Develop a concomitant condition which is given in the exclusion criteria but do attend a termination visit.

If a patient discontinues the study prematurely at any time after entering the study, attempts should be made to conduct a termination final visit at which time all of the assessments listed for the final visit will be performed.

The reason for premature discontinuation and – if applicable – the final visit will be documented.

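### The Step 3 check before rosiglitazone acts only on IHD and PVD, so known stage 1–2 heart failure does not by the printed rule keep a patient off the drug

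*Protocol article*

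**What the plan says.** The rule is in the Protocol article, Tablet arm, Step 3. Patients with HbA1c at 7% or above are to start rosiglitazone, subject to one prior check: "Before initiation of Rosiglitazone a repeat medical history will be taken with special emphasis on cardiovascular disease". One action is tied to that check: "if patients have a history of cardiovascular disease (defined as IHD, PVD) they will not be initiated on Rosiglitazone", and such patients go directly to Step 4 (insulin).

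Once the drug is started, two further rules apply. For monitoring: "Patients on rosiglitazone will be monitored using the adverse events form, for symptoms of heart disease specifically for chest pain and shortness of breath". For stopping: "Any adverse events suggestive of heart disease will result in Rosiglitazone being discontinued and the patient moving to step 4".

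Heart failure is named once, in the Exclusion criteria, item 16: "Patient has had stage 3–4 heart failure". Item 12 of the same list is discretionary. It covers significant conditions that, "in the opinion of the site investigator, are likely to affect" how the patient responds or whether the patient can finish the study.

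The section Withdrawn from study lists reasons for discontinuing treatment. They include a serious adverse event and this one: "Develop a concomitant condition which is given in the exclusion criteria but do attend a termination visit".

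**The concern.** The repeat history exists to keep patients with cardiovascular disease off rosiglitazone. What it acts on is a closed list, because the bracket says how cardiovascular disease is defined and does not merely give examples. Heart failure is not on that list, and the entry criterion that names heart failure starts at stage 3. Between the two rules lies a patient whose heart failure is known, is below stage 3, and is not accompanied by recorded IHD or PVD. The clinician taking the history would learn of the heart failure, and the printed rule would still lead to a prescription.

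What is at stake is the safety of those patients. The reason for concern is in the document: Step 3 treats cardiovascular history as a ground for not starting the drug, and events pointing to heart disease as a ground for stopping it, with breathlessness among the symptoms watched for.

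**Working it through.** The point is a comparison of rules. The little arithmetic only bounds its size.

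**Tracing one patient through the printed rules.** Take a patient with known heart failure below stage 3 (on whatever scale item 16 uses) and no IHD or PVD.

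| Stage | Rule | Outcome |
|---|---|---|
| Entry | Exclusion 16: stage 3–4 only | Not excluded |
| Entry | Exclusion 12: investigator's opinion | May or may not be excluded |
| Randomisation | Tablet arm | Steps 1 and 2 |
| Step 3 | HbA1c 7% or above | Rosiglitazone due |
| Before starting | Repeat history: IHD or PVD? | Neither, so no diversion |
| Start | 4 mg once daily | Drug given |
| On drug | Monitoring and stopping rule | Acts only after exposure |

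Only exclusion 12 can break this path before the first dose. The Withdrawn from study text does not close it either. A serious adverse event comes after exposure, and stage 1–2 heart failure is not itself a listed exclusion condition.

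**Can Step 3 be reached within 24 months?** Yes, from the Step 1 and Step 2 rules:
- Before month 3, if neither metformin nor Glucophage SR is tolerated.
- At month 3, if the patient entered on 2 g of metformin and HbA1c is above 7% three months later.
- By the longest route with HbA1c above 7% throughout and 3-monthly titration: 3 (lifestyle) + 4 × 3 (one, two and three tablets, then 2 g) = month 15.

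A patient first controlled on diet or metformin can reach Step 3 after month 15, and symptoms can prompt earlier up-titration.

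**Time on the drug.** If HbA1c stays at 7% or above, Step 3 lasts 3 + 3 = 6 months before Step 4, provided that it starts early enough to finish within the trial. If HbA1c is controlled on rosiglitazone and no adverse event stops it, exposure is 24 − 15 = 9 to 24 − 3 = 21 months. That range applies only to metformin-tolerant patients whose HbA1c was above 7% throughout Steps 1 and 2. It is not a range for the whole arm.

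**Number affected.** The Sample size section's 97 per arm reproduces from its own inputs (difference 0.7%, SD 1.5%, 90% power, two-sided 5%):

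2 × (1.960 + 1.282)² × (1.5/0.7)² = 96.5, rounded up to 97.

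The document gives neither the prevalence of stage 1–2 heart failure without IHD or PVD nor the share of patients reaching Step 3. With that share set to its maximum of 1 and no one excluded under item 12, each percentage point of prevalence gives 97 × 0.01 × 1 = 0.97 patients. This is a ceiling and not an estimate. The 97 counts analysable patients and is itself to be re-estimated from the first 30 recruited.

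**The case against.** The strongest objection is that the hazard is not in the document. Nothing there says that rosiglitazone harms patients with stage 1–2 heart failure, and a rule that stops a drug for new events does not prove that a stable prior condition should bar it. On this view the authors dealt with heart failure by severity at entry, added IHD and PVD as a drug-specific layer, and added monitoring as a third. Moving the line to any stage would then be a clinical preference.

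Part of this stands. The size of the hazard cannot be taken from the document, and none is asserted here. However, Step 3 itself makes cardiovascular history a reason to withhold this drug, and a history check that passes over known heart failure fits poorly with that purpose. Exclusion 16 applies to both arms at entry and is not a rule about rosiglitazone.

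Other safeguards narrow the group. Item 12 may remove some patients, and clinicians see all of them: "They are seen in secondary care at 3 centres in Wales". But item 12 turns on individual opinion about treatment response or study completion, formed before the arm is known, and monitoring begins only with exposure.

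Figure 2 and the full protocol are not shown and may hold a wider check. That limits confidence. It does not remove the point, because the printed sentence sets out its own definition.

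A reader might also infer that the start and stop rules contradict each other. They do not. One concerns history and the other concerns events on treatment, and both can be followed as written.

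**Conclusion.** The gap is real on the printed text. A tablet-arm patient with known stage 1–2 heart failure and no IHD or PVD, not excluded under item 12, would start rosiglitazone on reaching Step 3. This is a cheap improvement, held with moderate confidence.

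The number of patients is unknown and probably small, at most 0.97 per percentage point of prevalence among 97 analysable tablet-arm patients. The conclusion assumes that the bracketed definition is applied as written and that no wider check sits in the material not shown.

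Two stronger readings are not supported. The first is that the trial exposes patients to a demonstrated harm: the document neither states nor quantifies a risk in stage 1–2 heart failure. The second is that the primary comparison is affected: nothing in the document links this gap to a bias in the HbA1c or C-peptide result, and none is claimed.

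**What to change.** In the Step 3 sentence, extend the bracketed definition of cardiovascular disease so that it lists IHD, PVD and heart failure of any stage. Patients found to have heart failure at the repeat history would then move directly to Step 4, as those with IHD or PVD already do. If Figure 2 or the full protocol repeats the definition, it should match. Exclusion 16 need not change.

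The cost is one phrase. No new test or visit is needed, because the history check and the route to Step 4 already exist. The downside is that a few tablet-arm patients would skip the rosiglitazone step and start insulin earlier than they otherwise would.

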### Analysis plan

The statistical evaluation will be performed using SPSS. All data will be listed and trial summary tables will be provided. Summary statistics will be presented by group.

The primary analysis will be an intention to treat analysis examining (1) the average change in C peptide level at the end of the study in both groups and (2) the average change in HbA1c level at the end of the study in both groups. A linear regression model will be used to examine the effect of baseline GAD level, age, sex and baseline fasting C-peptide or HbA1c level as covariate and a treatment term on the change in HbA1c and C-peptide levels. In addition, repeated measures analysis (area under the curve, maximum minus minimum, time taken to maximum, time taken to minimum and slope) for C-peptide and HbA1c will be performed. ANOVA for repeated measurements with be used when variables are normally distributed. Otherwise, log transformations or non parametric tests will be employed.

Data will be collected by research nurses under the medical care of [name] and [name] and monitored by the trial co-ordinator. The analysis will be performed by [name] who will be blind to treatment group until after all analysis has been completed and interpreted. The CONSORT statement will be followed and used for reporting results.

Secondary analysis will include: Intention to treat analysis of :

(1) Average change in fasting C-peptide level in the insulin group compared to the control (best alternative care) group at 12 months.

(2) Average change in HbA1c level in the insulin group compared to the standard care group at 12 month. Data will be presented using confidence intervals only.

(4) Quality of life in the insulin vs standard care groups

(5) Number of events of fasting glucose being above 8 in the insulin vs standard care arm.

(6) Proportion of patients with a C-peptide below 0.38 ng/ml at baseline, 12 months and 24 months.

(7) Level of inflammatory markers in the insulin vs standard care arm

(8) GAD levels of insulin vs standard care

(9) Episodes of adverse events in the insulin vs standard care arms

(10) Weight gain in terms of BMI and waist/hip ratio in both groups

(11) HOMA or insulin resistance in both groups

We shall use two sided tests and confidence intervals for all comparisons.

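### Specific enquiry about chest pain and breathlessness is prescribed only in connection with rosiglitazone, which may inflate these two symptoms in the tablet arm unless all patients are asked the same questions

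*Protocol article*

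**What the plan says.** In the protocol article, Step 3 of the tablet arm introduces rosiglitazone and attaches a symptom check to it: "Patients on rosiglitazone will be monitored using the adverse events form, for symptoms of heart disease specifically for chest pain and shortness of breath". A finding has a treatment consequence: "Any adverse events suggestive of heart disease will result in Rosiglitazone being discontinued and the patient moving to step 4". Patients with a history of ischaemic heart disease or peripheral vascular disease do not start the drug and go straight to Step 4, where oral agents are stopped. Rosiglitazone exposure is therefore confined to Step 3.

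The text on the insulin arm and on tablet Steps 1, 2 and 4 contains no corresponding statement about cardiac symptoms.

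Under Analysis plan, the secondary list opens with "Secondary analysis will include: Intention to treat analysis of", and item (9) is "Episodes of adverse events in the insulin vs standard care arms". Under Design: "This trial is a multi-centre open parallel group prospective randomised trial". Follow up procedure sets visits every 3 months and states no difference between arms.

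**The concern.** Chest pain and shortness of breath are non-specific symptoms, and mild episodes may go unmentioned unless someone asks. If staff follow the text as written, the intensity of asking depends on treatment: it rises when a tablet-arm patient reaches Step 3 and is not described anywhere else. The results go onto the adverse events form, which presumably also supplies item (9).

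The analyst is to be blind to treatment group, but that protects the analysis and not the eliciting of events by staff and patients who know the treatment. An analysis plan written later could flag or set aside prompted events. It could not recover symptoms that other patients were never asked about, so collection has to be made even before data accrue.

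At stake is the fairness of one secondary safety comparison, mainly its chest-pain and breathlessness component.

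**Working it through.** **The plan's own figures.** The plan gives no event rate, reporting rate or share of patients reaching Step 3, so no stated figure bears directly on this point. The trial size does reproduce: 2 × (1.960 + 1.282)² × 1.5² / 0.7² = 96.5, or 97 per arm (Sample size: difference 0.7%, SD 1.5%, power 90%, two-sided 5%).

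**Assumptions.** True symptom rates are equal in the two arms. Capture without prompting is 50%. Capture with targeted enquiry is 80 to 100%. The share of tablet-arm follow-up spent on rosiglitazone is f. None of these is in the article.

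**Step 1: ratio while on the drug.** R = prompted capture / unprompted capture = 0.8/0.5 = 1.6, to 1.0/0.5 = 2.0.

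**Step 2: ratio between arms for these two symptoms.** 1 + f × (R − 1):

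| f | R = 1.6 | R = 2.0 |
|---|---|---|
| 0 | 1.00 | 1.00 |
| 0.2 | 1.12 | 1.20 |
| 0.4 | 1.24 | 1.40 |

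In patients, with an assumed 10% true risk, 97 per arm and R = 2.0, the insulin arm records 97 × 0.10 × 0.5 = 4.9. The tablet arm records 4.9 × 1.20 = 5.8 at f = 0.2 and 4.85 × 1.40 = 6.8 at f = 0.4.

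**Step 3: sensitivity to unprompted capture**, with prompted capture at 100%. At 30% unprompted, the ratio is 1 + 0.2 × (1/0.3 − 1) = 1.47 for f = 0.2 and 1.93 for f = 0.4. At 80%, it is 1.05 and 1.10. At 100%, it is 1.00 whatever f is.

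**Step 4: what f could be.** The slowest route takes 3 months of lifestyle change plus four 3-month metformin levels, 15 months in all. That leaves at most 9 of 24 months, or 37.5%. A patient who starts metformin at three tablets can reach Step 3 at about month 6 and, if then controlled, stay for 18 of 24 months, or 75%. A patient not controlled on rosiglitazone leaves after about 6 months, or 25%. Those controlled earlier, and those with the cardiovascular history above, contribute 0%. Averaged over the arm, 40% looks near the upper end, but the article does not fix it.

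**Step 5: all adverse-event episodes.** Item (9) counts every episode. If these two symptoms are a share q of episodes (assumed 5 to 10%), the overall ratio is 1 + q × (step 2 ratio − 1). At f = 0.4 this gives 1 + 0.05 × 0.24 = 1.012 to 1 + 0.05 × 0.40 = 1.020 for q = 5%, and 1.024 to 1.040 for q = 10%.

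**Step 6: after the change.** With equal capture in every patient R = 1, and the ratio is 1.00 for any f and q. The 97 per arm does not change.

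**The case against.** The strongest reply is that the Step 3 sentence is a safety instruction. It tells staff what to look for on the trial's existing form because a finding stops the drug. It does not say that other patients are not asked. Neither the form nor the visit-schedule figure is shown, and an article commonly leaves form content to the full protocol. This stands. A reader might infer that rosiglitazone patients are the only ones questioned, but the article does not say so, and if the form already asks everyone there is no bias.

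A reader might also infer that the tablet arm will show an excess from ascertainment alone. That is not supported either. The excess vanishes if routine capture is complete or if hardly anyone reaches Step 3. Stopping the drug after a suggestive event limits repeat counts under targeted enquiry, and keeping patients with cardiovascular history off rosiglitazone lowers the symptom rate among those monitored, although they still count in the tablet arm under intention to treat.

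The net direction is also open. Printed under the insulin treatment figure is: "Patients will be contacted weekly by phone in the first month, fortnightly in the second month and once a month thereafter". If that schedule is particular to insulin, it gives more occasions to record events there and works the other way. The tablet text mentions phone contact without a frequency.

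Finally, it is tempting to say that a true cardiac effect of rosiglitazone would be masked. Isolating such an effect is not an objective, and the drug's users are a non-randomised subset selected by their metformin response or tolerance and their cardiovascular history. Identical questions would not remove that selection.

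What survives is narrower: the text prescribes enquiry by treatment, item (9) compares arms, and nothing in the article says that the enquiry is common to both.

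**Conclusion.** The point holds as a risk and not as a demonstrated bias. Taken as written, the plan ties specific enquiry about two symptoms to a drug given in one arm of an open trial and then compares adverse-event episodes between arms. Under 50% unprompted and 80 to 100% prompted capture, the false ratio for these two symptoms is about 1.12 to 1.20 at 20% exposure and 1.24 to 1.40 at 40%. Those ratios should not be read as applying to item (9) as a whole, where the figure is about 1.01 to 1.04 at 40% exposure with a 5 to 10% symptom share. All of this rests on assumed capture rates, exposure and symptom share, and it is zero if the form already puts the same questions to everyone.

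Priority is low. The comparison is secondary, and HbA1c and fasting C-peptide are laboratory measures that this ascertainment does not directly affect. The change is worth making because it is cheap and cannot be made once the data are in.

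**What to change.** Put identical chest-pain and shortness-of-breath items on the adverse events form for every patient in both arms, asked at baseline and at each 3-monthly visit. State in the analysis plan that item (9) uses events collected through this common form and schedule, and that events found only through additional treatment-specific contact or enquiry, including extra phone calls, are listed separately. Leave the rosiglitazone monitoring and action rules as they are. If the form already asks everyone, one sentence saying so is enough.

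The cost is two questions per existing visit and one sentence in the analysis plan. Slightly more mild events will be recorded in the insulin arm and at the other tablet steps. The sample size is unaffected.
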